### Statistical analysis

A statistician blinded to the whole trial process will perform the statistical analyses using the SAS statistical software package (Version 9.1, SAS Institute Inc.) in the Computer Integrated Manufacturing System. For the evaluation of a curative effect in this trial, the full analysis set (FAS) will be used. The FAS is determined according to an intention-to-treat (ITT) population; all randomized patients who receive at least one treatment session will be included in the analysis set. The per-protocol analysis set (PPS) is defined as the patients who complete the study and do not have major protocol violations. Demographic data and other basic indicators will be analyzed to test the balance of the two groups at baseline. The main indicators and global indicators will be analyzed within the FAS and PPS. The results will be described with mean, standard deviation, median, P25 (percentile 25), P75 (percentile 75), maximum, and minimum values of the differences between the treatment period and the baseline period. Between-group differences will be tested using repeated measure analyses of the variance. The accepted level of significance for all analyses was *P* < 0.05. Considering the influences of other factors on the effectiveness, such as age, duration of disease, etc., these factors will be considered as covariants for the covariance analysis or logistic regression analysis when comparisons are made between the groups. Missing data will be replaced according to the principle of multiple imputations.

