**Methods/design:**

This study is a two-center, open-labeled, randomized, controlled trial. A total of 116 eligible patients with polycystic ovary syndrome will be randomly allocated in a 1:1 ratio to the electroacupuncture plus clomiphene citrate group or to the clomiphene citrate group. Participants in the electroacupuncture plus clomiphene citrate group will receive electroacupuncture treatment in addition to clomiphene citrate capsules, whereas participants in the clomiphene citrate group will be prescribed clomiphene citrate capsules only. Electroacupuncture treatment will be performed from the fifth day of menstruation or withdrawal bleeding until the next menstruation, in three sessions per week for three menstrual cycles. The primary outcome is the ovulation rate. The secondary outcomes include the dominant follicle rate, mean number of dominant follicles, endometrial thickness, time point of ovulation, follicular size before ovulation, luteinizing hormone, estradiol level, and pregnancy rate. The measuring points for outcomes will be baseline and the completion of treatment. Any adverse events occurring during the trial process will be recorded. In addition, a quality-monitoring group independent from the research team will be set up to control the quality of the trial.

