### Blinding

This is an open-labeled trial; therefore, neither the patients nor the clinical practitioners will be blinded for the entire process. However, in order to eliminate potential bias, other researchers, including data collectors and statisticians, will be blinded.

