### Interventions

Participants in the EA group will receive electroacupuncture treatment in addition to the oral administration of clomiphene citrate, whereas participants in the CC group will receive clomiphene citrate only. Treatment in both group will last three menstrual cycles. The intervention in this trial involves a rigorous acupuncture schedule. To ensure the compliance of acupuncturists to the schedule, we ask them to take pretrial training and an entrance exam for this trial. All included acupuncturists will have at least 2 years of practical experience in clinical acupuncture.

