#### Clomiphene citrate therapy

On the fifth day of menstruation, all participants, except for those with amenorrhea, will receive a pharmacological treatment regimen of 50 mg clomiphene citrate, taken once each day for 5 continuous days. Patients with amenorrhea will receive the same pharmacological treatment regimen after withdrawal bleeding has been induced by taking progestin. In cases of no ovulation, an additional 50 mg will be added to the dose in the next menstrual cycle. The maximum dose will not exceed 150 mg. The therapy will last for three menstrual cycles.

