#### Electroacupuncture

In order to increase the reproducibility and internal validity of the trial, electroacupuncture treatment will be applied to PCOS patients. As the stimulation of electroacupuncture can be more quantifiable relative to manual acupuncture, its employment may reduce the risk of bias somewhat. Sanyinjiao (SP 6), Guanyuan (BL 26) Zhongji (CV 3), and Zigong (EX-CA 1) have been chosen for the formula of compulsory acupoints. Additionally, sets of three arbitrary points will be alternately selected according to the phase of the menstrual cycle: Taichong (LR 3) and Taixi (KI 3) will be needled after menstruation; Mingmen (GV 4) and Xuehai (SP 10), during the ovulatory period; and Xuehai (SP 10) and Geshu (BL 17), before the next menstruation.

Each acupoint will be needled using a filiform needle (25–50 mm in length and 0.25 mm in diameter) to achieve a *Deqi* sensation (refers to a sensation of numbness, distension, or electrical tingling at the needling site and might radiate along the corresponding meridian). Then, an auxiliary needle (13 mm in length and 0.18 mm in diameter) will be inserted, 2 mm lateral to the first needle, to a depth of 2 mm without achieving *Deqi*. Electrical stimulation will be applied at every acupoint, with one electrode connected to the filiform needle and the other to the auxiliary needle. This method circumscribes the electrical stimulation nearby, rather than going across the human body surface to cause performance bias. Electrical stimulation will last for 30 min in each acupuncture session. Electroacupuncture treatment will be performed three times per week from the fifth day of menstruation or withdrawal bleeding until before the next menstruation for three menstrual cycles.

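### The full analysis set is called intention-to-treat but requires a treatment session, a unit that fits only the electroacupuncture arm, so exclusions can differ by arm

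*Protocol article*

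**What the plan says.** All of the following is in the protocol article.

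- **Statistical analysis:** "For the evaluation of a curative effect in this trial, the full analysis set (FAS) will be used". On its basis: "The FAS is determined according to an intention-to-treat (ITT) population". The same sentence then gives the entry rule: "all randomized patients who receive at least one treatment session will be included in the analysis set". The only other set is a per-protocol set, which is narrower. Missing data are to be multiply imputed.
- **Abstract, Methods/design:** electroacupuncture is given "in three sessions per week for three menstrual cycles".
- **Electroacupuncture:** "Electrical stimulation will last for 30 min in each acupuncture session".
- **Interventions:** "participants in the CC group will receive clomiphene citrate only".
- **Clomiphene citrate therapy:** the drug is "taken once each day for 5 continuous days".
- **Blinding:** "neither the patients nor the clinical practitioners will be blinded for the entire process". Data collectors and statisticians are to be blinded.

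**The concern.** An intention-to-treat set is fixed by randomisation alone. This one also depends on something that happens afterwards, so its label and its rule disagree.

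The condition is also stated in a unit that belongs to one arm. An EA woman who takes her clomiphene but attends no needling may be dropped for lack of a session, while a CC woman who takes the same capsules is kept. Two statisticians working from this sentence could build different populations for the main comparison.

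Dropping non-starters does little harm when knowledge of the arm cannot influence starting. Here the woman and her practitioner both know the arm, and three needling visits a week over three cycles ask far more of her than capsules do. If starting depends on the arm and is also related to the chance of ovulating, the two retained groups are no longer comparable by design.

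Two features of the plan do not repair this. Multiple imputation fills gaps for women inside the set and does not readmit those outside it. Blinding data collectors and statisticians does not undo an exclusion that the rule itself requires.

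**Working it through.** **1. The wording.** The article gives no count of expected non-starters, so there is no figure of its own to reproduce. The main check is textual.

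| Element | EA arm | CC arm |
|---|---|---|
| Treatment (Interventions) | Electroacupuncture plus clomiphene | Clomiphene only |
| Is a session defined? | Yes: 30 minutes, three per week | No: daily capsules over 5 days |
| FAS entry rule (Statistical analysis) | At least one session | At least one session, with no stated meaning |

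Apart from the FAS sentence, session refers to electroacupuncture wherever it appears. No set of all randomised women is described.

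**2. What arm-specific exclusion could do.** This is an illustration.

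From the article (Sample size calculation): 58 women per arm, 55% ovulation expected on clomiphene, a planned difference of 75% - 55% = 20 points, and a 15% dropout allowance.

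Assumed, with no support in the article: x of the 58 EA women are dropped, none are dropped from CC, and the dropped women would ovulate at rate q. Under no true effect the whole randomised EA arm ovulates at 55%, that is 0.55 × 58 = 31.9 expected ovulators.

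Retained EA rate = (31.9 - q·x) / (58 - x). Shift = retained rate - 0.55 = x(0.55 - q) / (58 - x).

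| x | q | Retained EA rate | Shift (points) |
|---|---|---|---|
| 5 | 0.20 | (31.9 - 1.0)/53 = 0.583 | +3.3 |
| 5 | 0.40 | (31.9 - 2.0)/53 = 0.564 | +1.4 |
| 5 | 0.55 | (31.9 - 2.75)/53 = 0.550 | 0 |
| 8 | 0.20 | (31.9 - 1.6)/50 = 0.606 | +5.6 |
| 8 | 0.40 | (31.9 - 3.2)/50 = 0.574 | +2.4 |
| 8 | 0.55 | (31.9 - 4.4)/50 = 0.550 | 0 |

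The shift is zero when x = 0 or q = 0.55, and negative when q exceeds 0.55. Against 20 planned points, the non-zero rows run from 1.4/20 = 7% to 5.6/20 = 28%. Eight women is close to the whole dropout allowance (0.15 × 58 = 8.7), so it is an upper scenario.

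**3. Effect on the false-positive rate.** This uses the same null, exclusions in EA only, and a plain two-sided comparison of two proportions at 0.05 (normal approximation). Removing 10% of the EA arm (0.10 × 58 = 5.8 women) gives a rejection probability of 0.053 with q = 0.40 and 0.069 with q = 0.20. Removing 15% (8.7 women) gives 0.059 and 0.098. With q = 0.55 it stays at 0.050.

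**The case against.** The strongest reply is that the authors meant one rule for both arms: any treatment received. The sentence speaks of a treatment session, not an acupuncture session, applies it to all randomised patients, and the article calls clomiphene a treatment too. A full protocol or analysis plan, not shown here, could say how the rule works for capsules. This intention is likely. It does not remove the defect, because the rule is printed in full with a unit that CC women do not have, and even the generous reading conditions on a post-randomisation event under an intention-to-treat label.

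The reply does defeat some stronger readings:

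- **That no CC woman qualifies.** The letter of the rule gives this, but it would leave no comparison and cannot be intended.
- **That exclusions do differ by arm.** The article supports only that they can.
- **That women wait weeks between allocation and treatment.** Overview of the study design puts randomisation after consent, and treatment starts on day 5 of a natural or induced bleed. Nothing says where randomisation falls relative to that bleed, or whether progestin comes before or after it. A long wait is possible but not documented.

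The assumed 20-40% is also open to challenge. EA women who skip needling but take clomiphene would be expected, on the article's own figures, to ovulate at about 55-59%. At 55% the shift is zero. At 59% it is slightly negative: 5 × (-0.04)/53 = -0.4 points, or 8 × (-0.04)/50 = -0.6 points. Lower rates suit women who take nothing, and an any-treatment rule would exclude those from both arms. This objection stands, so the non-zero figures show what is possible and are not a forecast.

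**Conclusion.** The point holds as a defect in a stated rule. The set used for efficacy carries an intention-to-treat label, is conditioned on a post-randomisation event, and has no workable entry criterion for the control arm. In a trial with unblinded patients and practitioners, exclusions can therefore differ by arm.

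The bias itself is not established. A reader might infer that the comparison has lost the protection of randomisation. The article supports less: that protection is weakened only so far as women fail to start, the rule removes them unequally, and starting is related to outcome. The shifts of 1.4-3.3 points (5 dropped) and 2.4-5.6 points (8 dropped) rest wholly on assumed counts, assumed rates of 20-40% and no exclusions in CC. Zero is also compatible with the article. Confidence is high on the wording and low on any size or direction. This should be fixed.

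**What to change.** Define the FAS as all randomised women, analysed in the arm assigned, whether or not treatment began. Handle absent ovulation data by the multiple imputation already planned, and add a sensitivity analysis that counts missing as not ovulated. If a started-treatment set is wanted, keep it as a sensitivity set with a single criterion that can be met in either arm, for example having taken the first clomiphene dose.

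The text change is small: the definition and a line on sensitivity analyses. The statistical price is that a few non-starters stay in and slightly dilute the estimate. In practice, ovulation outcomes should be sought from non-starters too, which takes some follow-up effort. According to Trial status, recruitment had not begun at submission, when the change would have been almost free. Made after outcome data are seen, it would look like a post hoc choice of population.

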#### Secondary outcomes

The secondary outcomes will include the dominant follicle rate, mean number of dominant follicles, endometrial thickness, time point of ovulation, follicular size before ovulation, luteinizing hormone (LH) level, estradiol (E2) level, and pregnancy rate.

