#### Time points of outcome measurement

Outcomes will be assessed at two time points: baseline and the completion of the treatment. Furthermore, patients will be given some regular tests at baseline, including routine blood tests, liver function test, and kidney function test. The overview of the outcome measurement at the different time points is shown in Table 1.

**Table 1 Tab1:** Trial process chart

Time point	Baseline	Post-treatment
Diagnosis		
Inclusion confirmed	✓	
Informed consent signed	✓	
Body sign	✓	✓
Disease history	✓	
Treatment history	✓	
Comorbidity	✓	✓
Current treatment	✓	✓
Outcome assessment		
B ultrasound	✓	✓
Follicle-stimulating hormone	✓	✓
Luteinizing hormone	✓	✓
Testosterone	✓	✓
Estradiol	✓	✓
Blood HCG	✓	✓
Regular tests		
Routine blood tests	✓	
Liver function test	✓	
Kidney function test	✓	
Data collection and statistical analysis		
Adverse event		✓
Causes of dropout		✓
Safety analysis		✓
Compliance analysis		✓

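### LH and estradiol (and endometrial thickness, if recorded at baseline) are to be tested by repeated-measures ANOVA; adding each outcome's own baseline to the covariance analysis already planned would be more precise at no cost

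*Protocol article*

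**What the plan says.** Under Time points of outcome measurement the article sets the schedule: "Outcomes will be assessed at two time points: baseline and the completion of the treatment". Table 1 ticks luteinizing hormone, estradiol and B ultrasound in both columns. Endometrial thickness is a listed secondary outcome but has no row of its own in Table 1. That it is measured at baseline follows only from the B ultrasound row and the general sentence just quoted.

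The Statistical analysis section then does three things in turn:

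- It describes results by summary statistics, ending with "maximum, and minimum values of the differences between the treatment period and the baseline period". This is change from baseline.
- It names the test: "Between-group differences will be tested using repeated measure analyses of the variance".
- It adds an adjusted analysis: "Considering the influences of other factors on the effectiveness, such as age, duration of disease, etc., these factors will be considered as covariants". The sentence goes on to say that these enter a covariance analysis or a logistic regression when the groups are compared.

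The outcome's own baseline value is not named as a covariate. The section does not say how the repeated-measures test and the covariance analysis relate, or which carries the conclusion.

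**The concern.** With one value before treatment and one after, repeated-measures ANOVA offers nothing beyond a comparison of changes. Subtracting the whole baseline value corrects by the right amount only when baseline and post-treatment values are almost perfectly correlated. At lower correlations it adds noise. With equal SDs and a correlation below 0.5, the change score is less precise than ignoring the baseline altogether. Regressing the post-treatment value on the baseline lets the data set the amount of correction.

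The Background and the Discussion both give effects on sex hormones as part of the trial's purpose, so LH and estradiol matter to its conclusions. At stake is the width of their confidence intervals, and the chance of detecting a real effect, with a baseline measurement that is already being taken.

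**Working it through.** **Figures available.** The article claims no power for LH, estradiol or endometrial thickness, so there is no figure of the plan's own to reproduce. From the Sample size calculation section I take only the group sizes, 58 recruited and 50 evaluable per arm; how 50 was derived is a separate matter. Alpha is 0.05 ("The accepted level of significance for all analyses was *P* < 0.05"), taken here as two-sided because the article does not say.

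**Assumptions not in the article.** The baseline-to-post correlation rho is shown over a range. The true difference is set at 0.5 SD. SDs are taken as equal at both times and in both arms.

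**Step 1: equivalence.** With two time points, the group-by-time contrast is (post − pre) in one arm minus (post − pre) in the other. Its test is the two-sample t test on change scores.

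**Step 2: variance per participant, in units of the outcome's variance.**

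- Change score: 1 + 1 − 2rho = 2(1 − rho)
- Post-treatment value adjusted for baseline: 1 − rho²
- Ratio, ANCOVA to change score: (1 − rho²) / [2(1 − rho)] = (1 + rho)/2

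The ratio is below 1 for every rho below 1. At rho = 0.5 the change score has variance 2(0.5) = 1, the same as the post-treatment value alone. Below 0.5 it is worse than that.

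**Step 3: power.** The noncentrality parameter is 0.5 / √(2v/n), where v is the variance from step 2, referred to a noncentral t distribution. Example at n = 58 and rho = 0.5: the change score gives 0.5/√(2×1/58) = 2.69, power 76%; ANCOVA gives 0.5/√(2×0.75/58) = 3.11, power 87%.

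| rho | Variance, change | Variance, ANCOVA | Ratio | Power at 58 per arm, change vs ANCOVA | Power at 50 per arm, change vs ANCOVA |
|---|---|---|---|---|---|
| 0.3 | 1.40 | 0.91 | 0.65 | 62% vs 80% | 55% vs 74% |
| 0.5 | 1.00 | 0.75 | 0.75 | 76% vs 87% | 70% vs 82% |
| 0.7 | 0.60 | 0.51 | 0.85 | 93% vs 96% | 89% vs 93% |

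In terms of patients, a change-score analysis of 50 per arm is worth an ANCOVA of 50 × 0.65 = 32.5, 50 × 0.75 = 37.5 or 50 × 0.85 = 42.5 per arm. At rho = 0.9 it is worth 47.5, and the difference hardly matters.

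**Step 4: check by simulation.** With 4,000 simulated trials of 50 per arm at each rho, the variance ratios were 0.66, 0.74 and 0.86, against 0.65, 0.75 and 0.85 from the formula. Estimating the slope in a trial of this size therefore costs almost nothing.

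**The case against.** The strongest reply is that a covariance analysis is already planned and its covariate list is open, so the baseline value may be intended, and a full list belongs in a document not shown. The first part stands: it would be wrong to say that the plan does not adjust at all. But the open list commits the trial to nothing, and repeated-measures ANOVA is a stated choice of test rather than a detail left for later.

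A second reply is that a change-based comparison is legitimate. It is: under randomisation it is valid and unbiased. Only efficiency is in question.

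A third is that the gain is unknown, because the article gives neither rho nor an SD. That also stands. On the assumptions used, the gain at 58 per arm runs from about 18 percentage points of power at rho = 0.3 to about 3 at rho = 0.7.

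A reader might go further and infer that the treatment estimate will be diluted by half, taking the between-group wording to mean the group main effect averaged over both times. The article does not support that. It names no model term, and the sentence just before the test describes differences from baseline, which points to the group-by-time comparison.

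**Conclusion.** The point holds as one of precision on secondary outcomes. For LH and estradiol, the named test has a larger variance than a baseline-adjusted comparison at any rho below 1. The ANCOVA variance is 35% lower at rho = 0.3, 25% lower at 0.5 and 15% lower at 0.7. The same applies to endometrial thickness if it is recorded at the baseline ultrasound. The ratios rest on equal SDs and an assumed rho; the power figures also rest on an assumed 0.5 SD difference and two-sided testing.

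It does not follow that the planned test is invalid, or that it would bias the hormone results. The ovulation rate and the sample size based on it are not touched. The change is worth making because it is free, and because the article reports that the trial had not begun at submission, so it could be made before any data were seen.

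**What to change.** In the Statistical analysis section, make the covariance analysis already planned the between-group test for LH and estradiol, and for endometrial thickness if it has a baseline value. Specify the post-treatment value as outcome, treatment arm as factor, and the same variable's baseline value as a covariate alongside age and duration of disease. Use the log scale for the hormones if they are skewed. Report the adjusted difference between arms with its 95% confidence interval, and keep change from baseline as description only. State in Table 1 whether endometrial thickness is recorded at the baseline ultrasound.

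The cost is a sentence or two of wording. LH and estradiol are already scheduled at both times, so no patients, visits or hormone measurements are added.

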### Participants

We plan to recruit patients with PCOS diagnosed on the basis of *Revised 2003 Consensus on Diagnostic Criteria and Long-Term Health Risks Related to Polycystic Ovary Syndrome* established by The Rotterdam ESHRE/ASRM-Sponsored PCOS Consensus Workshop Group [19]. According to these criteria, women with two out of three of the following items can be diagnosed as having PCOS: (1) oligoovulation or anovulation, (2) clinical and/or biochemical signs of hyperandrogenism, and (3) polycystic ovaries and exclusion of other etiologies (congenital adrenal hyperplasia, androgen-secreting tumors, Cushing’s syndrome). Further assessment of eligibility is based on the inclusion and exclusion criterion as follows.

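### Time of ovulation and pre-ovulatory follicle size are undefined in women who do not ovulate, yet the analysis and imputation rules make no exception for them

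*Protocol article*

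**What the plan says.** The Protocol article's Secondary outcomes section includes "time point of ovulation, follicular size before ovulation" in its list.

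The Statistical analysis section then sets rules that are not tied to particular outcomes:

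- Analysis set: "all randomized patients who receive at least one treatment session will be included in the analysis set". Women who never ovulate are therefore in it.
- Summary: descriptive statistics, ending with the "maximum, and minimum values of the differences between the treatment period and the baseline period".
- Test: "Between-group differences will be tested using repeated measure analyses of the variance". Covariance analysis or logistic regression is added for covariates such as age and disease duration.
- Missing values: "Missing data will be replaced according to the principle of multiple imputations".

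Under Time points of outcome measurement: "Outcomes will be assessed at two time points: baseline and the completion of the treatment". The Sample size calculation expects ovulation in 75% of the electroacupuncture (EA) arm and 55% of the clomiphene (CC) arm.

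The article does not separate a value that is undefined because ovulation did not occur from a value that was simply not recorded.

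**The concern.** A woman who does not ovulate has no ovulation time and no follicle size preceding ovulation. The written rules can be applied to her in two ways, and neither gives a sound randomised comparison.

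- **Impute.** The imputation model would borrow from ovulators to supply a time and a size for an event that did not take place.
- **Omit.** The comparison is then between ovulators in each arm. Ovulation is the primary outcome, and the trial expects treatment to change it, so the two subsets are selected differently and randomisation no longer protects the contrast.

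The change-from-baseline summary adds to the difficulty, because many women in this population will have no ovulation at baseline to measure. At stake is the interpretation of two secondary outcomes, each tested at the 0.05 level. A difference between arms on either could reflect which women ovulated and not any effect on timing or follicle growth.

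**Working it through.** **Inputs from the Protocol article.** Expected ovulation 75% (EA) and 55% (CC); 50 women per arm required and 58 recruited to allow for 15% dropout (Sample size calculation). The plan gives no figure for the number of women without a value, so there is none to reproduce.

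**Step 1. Women with no value, counting ovulation once per woman.** Number = n × (1 − rate).

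| n per arm | EA | CC |
|---|---|---|
| 58 | 58 × 0.25 = 14.5 | 58 × 0.45 = 26.1 |
| 50 | 50 × 0.25 = 12.5 | 50 × 0.45 = 22.5 |

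The imbalance of 20 percentage points follows from the trial's own hypothesis.

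**Step 2. Ovulators-only comparison when treatment has no effect on the measure.** Assumption: a latent standard-normal tendency to ovulate, U, with ovulation when U exceeds a threshold that gives the arm's rate p. The measure has unit SD over all women and correlation rho with U. The documents give no rho, so a range is shown.

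- Mean of U among ovulators = phi(c)/p, with c = z(1 − p).
- EA: c = −0.674, 0.3178/0.75 = 0.424. CC: c = −0.126, 0.3958/0.55 = 0.720.
- Spurious difference = rho × (0.720 − 0.424) = rho × 0.296.
- Rejection rate: two-sided t test at 0.05, 8,000 simulated trials per setting, 58 randomised per arm.

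| rho | Spurious difference (SD) | Rejection rate |
|---|---|---|
| 0 | 0 | 5.0% |
| 0.3 | 0.09 | 6.6% |
| 0.5 | 0.15 | 10.9% |
| 0.7 | 0.21 | 16.8% |

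**Step 3. The opposite extreme: follicle size alone determines ovulation.** Assumption: size X is normal with SD 1, and ovulation occurs when X > 0. Then the arm mean is mu = z(p), and the mean among ovulators is mu + phi(mu)/p.

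- True shift: 0.674 − 0.126 = 0.549 SD.
- Ovulators: EA 0.674 + 0.424 = 1.098; CC 0.126 + 0.720 = 0.845 (from unrounded terms).
- Observed difference: 1.098 − 0.845 = 0.253 SD, so 1 − 0.253/0.549 = 54% of the shift is lost.

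The ovulators-only contrast can thus show a difference where there is no effect, or understate one that exists, depending on a mechanism that the data will not reveal.

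**Step 4. Baseline values.** The Participants section requires two of three features, beginning "1) oligoovulation or anovulation, (2) clinical and/or biochemical signs of hyperandrogenism", the third being polycystic ovaries. Women who qualify through anovulation have no baseline ovulation time or pre-ovulatory size. Oligo-ovulatory women may have one, as may women who qualify on the other two features alone.

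**The case against.** The strongest reply is that the article never says a non-ovulator's ovulation time counts as missing. If it is undefined, the imputation sentence need not reach it, and handling by outcome is ordinary content for an analysis plan that is not shown here. Part of this stands: a reader might infer that the investigators have decided to impute ovulation times, or to drop non-ovulators, and the article states neither. But the point does not rest on silence. The article states general rules on analysis set, change score, test and imputation, and they do not fit two outcomes that it names. Covariance analysis and logistic regression are offered for covariate adjustment and do not solve this.

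Four stronger readings are tempting but unsupported:

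- *No woman has a baseline value.* The diagnostic criteria admit women who ovulate at least sometimes, so only many, not all, lack one.
- *About 35% of women will have no value.* This is (14.5 + 26.1)/116. It assumes no dropout and one ovulation status per woman. Treatment spans three cycles, and the article does not say whether the rate is per woman or per cycle. The imbalance between arms arises either way.
- *The trial will lose 54% of a follicle-size effect, or see it reversed.* The 54% belongs to the one-threshold model of Step 3, which covers follicle size only. In that model the sign is preserved, so it shows attenuation and not reversal.
- *A follicle measure available in every woman could replace the listed outcome at no cost.* Table 1 shows ultrasound only at baseline and post-treatment, so the article does not establish the serial scans that this would need. Replacing a listed outcome is also more than a wording change.

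**Conclusion.** The concern holds for these two secondary outcomes. As written, the rules lead either to imputed values for events that did not occur or to a comparison of subsets selected after randomisation on an outcome that treatment is expected to change.

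The expected share without a value, 25% against 45%, rests on the plan's own rates and on counting ovulation once per woman. The size and direction of any bias are unknown. The 0.09 to 0.21 SD spurious difference and the rejection rate of about 7% to 17% are illustrations under an assumed latent-normal model with assumed correlations; the shrinkage from 0.55 to 0.25 SD is an illustration under a different assumption. None is an estimate for this trial.

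A reader might infer that the main result is compromised. It is not on this ground: ovulation itself is defined for every woman. The point should be corrected before analysis but does not threaten the primary comparison.

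**What to change.** Three changes to the Statistical analysis section:

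1. State that multiple imputation applies only to values that exist but were not recorded, and that a value undefined for lack of ovulation is not imputed.
2. Analyse time to ovulation in all randomised women as time-to-event, from the start of the cycle, censoring women who do not ovulate at the end of cycle follow-up. Use a log-rank test or Cox model, with robust standard errors if several cycles per woman are used. Define the censoring time so that it also works for a woman who has no next menstruation.
3. Report pre-ovulatory follicle size among ovulators descriptively, with the number of ovulators per arm and no between-arm P value. Do not require a baseline value for either outcome.

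Optionally, if scans are in fact taken in each cycle, add maximum follicle diameter in all women as an exploratory measure.

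The cost is mainly wording. Recording an ovulation time already requires cycle tracking, and the clomiphene dosing rule already depends on ovulation status in each cycle. The price is that one secondary outcome loses its formal test and the time-to-ovulation analysis overlaps with the primary outcome, so it should not be read as independent confirmation. The article reports that the trial had not begun at submission.
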